### Outcome measures

The primary outcome will be the efficacy of riluzole as a means of reducing spasticity. The description of this main outome will be binary (success or failure). Success has been defined as follows: “Improvement of the Modified Ashworth Scale (MAS) score by more than 1 point, or improvement of the 0–10 Numerical Rating Scale (NRS) spasticity score by more than 20% between Week 0 and Week 2”.

The MAS is the most commonly used clinical method of measurement for assessing spasticity [1]. This score measures the resistance perceived by the rater when passively moving a joint through its full range of movement. MAS scores will be assessed by an experienced clinician on at least the adductor and/or triceps surae muscles at screening, randomization, end of treatment and follow-up visits [51]. The Minimal Clinically Important Difference in MAS lower limb muscles is 0.73 [52].The 0–10 NRS score (0 = “no spasticity” to 10 = “wo8rst possible spasticity”) is a participant-reported outcome measure designed to reflect participants’ perception of their spasticity. This score has been previously used on SCI participants and has been validated for Multiple Sclerosis spasticity assessment purposes [53]. The 20% cut-off was chosen because the Minimal Clinically Important Difference in the NRS is 18% [53]. The 0–10 NRS score will be assessed by each participant at screening, randomization, during the treatment period (every 24 hours) and at the follow up visits. The patients will be asked to record their scores in the “drug and 0–10 NRS” diary.

These two scales assessed by either the participant (NRS) or the clinician (MAS) will allow us to have a clearer picture and a greater sensitivity to the changes in spasticity before versus after the treatment period.

Secondary outcomes will include neurological, functional, and pain outcomes such as:

Penn Spasms Frequency Scale: This is a self-reported perception of patients’ spasticity based on frequency ratings (from 0 = no spasms to 4 = spasms occurring more than ten times per hour) and severity ratings (1 = mild to 3 = severe) of their spontaneous muscle spasms. This tool is widely used to complement clinical assessments of spasticity and provide a more comprehensive understanding of an individual’s spasticity status [54].Participant Global Impression of Change: This scale is a 7-point categorical scale rated by the participant from 1 (very much improved) to 7 (very much worse). Participants are asked to assess the overall change in their condition since joining the study.Visual Analog Pain Scale: This scale is an 11-point continuous scale rated by participants from 0 (no pain) to 10 (worst possible pain).Neuropathic Pain Symptom Inventory: This questionnaire can be used by clinicians to classify various types of neuropathic pain and assess the changes induced by pharmacological treatment. This scale includes: 10 descriptors of various symptoms and 2 items quantifying the duration of spontaneous ongoing and paroxysmal pain. A total intensity score can be calculated as the sum of the scores obtained on the 10 descriptors [55].DN4 questionnaire: This questionnaire can be used by clinicians to discriminate between nociceptive and neuropathic pain. This scale has been validated with a high level diagnostic accuracy for use on individuals with SCI [56]. A score of three or more indicates neuropathic pain [57]. This questionnaire will be applied at the screening visit.International Spinal Cord Injury Basic Pain Data Set: This questionnaire contains a minimal amount of clinically relevant information about pain that can be collected in the everyday practice of healthcare professionals’ with experience of SCI. This questionnaire applies to all the effects of pain (how it interferes with patients’ day-to-day activities, their overall mood, and their ability to get a good night’s sleep) rating from zero (no interference) to six (extremely strong interference), specifying the number of pain-related problems and a description of the worst 3 [58].Spinal Cord Injury Independence Measure: This measure addresses three specific types of functional problems in participants with SCI, including an assessment of self-care problems (feeding, grooming, bathing, and dressing), respiratory and sphincter management, and the participant’s mobility levels (getting in and out of bed and going indoors/outdoors) [59]. The participant’s score is rated here by the clinician.Personal therapeutic objectives: Personal objectives will be determined at baseline (e.g. Adductor muscle spasticity, etc.) by the clinician along with the participant.Electrophysiology: A nerve conduction study and an Electromyography (EMG) will be performed using standard techniques. The tibial nerve will be stimulated at the ankle and popliteal fossa, and compound muscle action potentials (M-Wave) will be recorded over the abductor hallucis. Measurements include negative peak duration, baseline-to-peak amplitude, mean F-wave amplitude and soleus H reflex. The maximal H-reflex and M-wave responses can be used to compare maximum H-reflex amplitude and maximum M-wave amplitude (Hmax/Mmax) ratios between subjects under different recording conditions. Surface EMG will be performed at experienced centers only. Subjects will be seated in an adjustable chair with their test foot securely strapped to an instrumented footplate attached to a mechanical fixture. Surface electrodes will be attached to the skin above the muscle in order to measure the activity in the right and left tibialis anterior and soleus muscles. The EMG signal will be amplified and filtered (3Hz–3kHz, GRASS P511K). Electrophysiology examinations will be performed before drug intake and 2h post dose on Day 1 and Day 14.Riluzole pharmacokinetics (PK): Riluzole concentration in plasma is quantified by performing a high performance liquid chromatography assay with U.V. detection, adapted from Chow et al. [46], after a liquid-liquid extraction step from a 200-μl plasma sample. The assay is linear from 5 to 500 ng/ml, with a lower quantification limit of 5 ng/ml. For wash-out checking purposes, baclofen concentrations in plasma will be quantified by performing a liquid chromatography-tandem mass spectrometry assay (LC-MS/MS) after a solid-liquid extraction step. The assay is linear from 2 to 200 ng/ml, with a lower quantification limit which has been validated at 1 ng/ ml. The plasmatic concentrations of baclofen after IT administration can be expected to be low [60]. All the participants enrolled in the study will be asked to donate optional blood samples. These specimens will be used for research purposes to identify and/or check the presence of any inherited DNA polymorphisms known or thought to be associated with riluzole activity, which will be taken for DNA extraction from relevant participants after receiving their genetically informed consent at the predose stage.Safety and tolerability: to be assessed by the occurrence of Adverse Events (AE). All suspected unexpected serious AE are to be notified immediately to the sponsor.Laboratory safety parameters: Participants will undergo laboratory screening analysis including haematology (red blood cell count, Hematocrit, Hemoglobin, white blood cell count, platelets), biochemistry (sodium, potassium, chloride, calcium, phosphorus, lactic dehydrogenase, creatine phosphokinase, alkaline phosphatases, amylase, lipase, gamma-glutamyl transferase, total and conjugated bilirubin, creatinine, urea, uric acid, glucose, albumin, total proteins, total cholesterol, triglycerides), serologies (hepatitis B antigen, Hepatitis C antibodies, Anti-HIV1 and Anti HIV2 antibodies) and urinalysis (proteins, glucose, blood, ketone bodies, pH). All analyses will be performed by a local laboratory.Bladder diary: The participants will record in a diary the frequency of urinary probing and urinary leakages during 1 day during the 3 days preceding visit 2 (randomization) and during the 3 days preceding visit 4 (end of treatment).

### Risks and unblinding procedures

Results of previous studies on patients with amyotrophic lateral sclerosis have shown that the overall tolerability of riluzole is good [61] and that the drug can be used on all patients except for those with elevated transaminase levels or active liver disease. The most frequently encountered AEs are asthenia, gastrointestinal disorders, nausea and dizziness, which were more frequent at the 200-mg dose. The occurrence of these same AEs, although at a lower frequency, has also been reported in Phase IV observational studies and pharmacovigilance surveys. No unexpected AEs clearly associated with riluzole have been observed. A risk less commonly reported, but still very serious, is that of neutropenia, and physicians should watch out for this risk.

If any cases arise in which the spasticity worsens under treatment, the investigator will search for an intercurrent condition that is likely to explain this aggravation, including: infection, lithiasis, fecaloma, bedsores, etc. In the case of patients undergoing intrathecal baclofen infusions (phase 2b), the investigator will first check the pump. These conditions have first to be treated. In cases where no specific condition has been identified or the spasticity does not improve after treatment of the intercurrent condition, the administration of the experimental drug will be stopped.

Unblinding procedures: the need to unblind participants to their status can arise in the following cases:

To make decisions about a patient’s clinical treatment or when an unexpected serious AE occurs and the intervention must be made known. If required, the investigator may apply to the sponsor for unblinding, with the coordinator’s approval,At the request of the Data Safety Monitoring Board,During an unmasked analysis in keeping with the study analysis plan.

Only the FCRIN platform and the clinical trial’s pharmacy team at the Timone hospital will be unblinded and will handle the unblinding procedures.

### Data management

In this trial, relevant data, AE, and safety assessments will be documented in both paper and electronic versions of the case report forms. Each participant has a unique numeric identifier. Data will be recorded and managed using a dedicated web-based software REDCap (Research Electronic Data Capture) with secured and restricted access. No personal data will be recorded in the case report forms apart from the unique numeric identifier. Access to the complete final trial dataset will be restricted to the clinical research unit’s statistician, who will analyse the study data for the purpose of reporting and publication of the results.

### Monitoring

The Data safety monitoring board, with no interests in either the drug tested or research on this drug, will be set up by the sponsor and entrusted with the mission of following up the security data. The Data safety monitoring board will also have an advisory function on points of security such as the tolerance and the reassessment of the benefit-to-risk ratio during the research process. This committee will also be responsible for making sure of the conformity of the protocol with current standards. The DSMB will meet at the end of Step 1. In the event of any anomaly, this committee will meet again as appropriate.

### Statistical analysis

Bayesian analysis will be performed by the CIC-EC 1426/FCRIN PARTNERS platform. Secondary analysis and safety analysis will be performed by the CIC-CPCET. Quantitative variables will be expressed as medians (quartiles) or means (standard deviations), depending on whether or not there is a Gaussian distribution. Qualitative variables will be expressed as numbers (percentages). Inter-group comparisons will be conducted using parametric or non-parametric tests, depending on the nature and the distributions of the variables. Unless otherwise specified, statistical significance is defined here as p<0.05. Baseline value will be the last value recorded before randomization. In phase 1b, all participants with whom the primary endpoint has been reached will be analysed with a view to applying the continuous reassessment method. In phase 2b, the probability of a response being associated with the minimum effective dose will be estimated using a Bayesian approach according to a beta-binomial model. Statistical analyses will be performed sequentially per participant at the end of the 2-week assessment period.

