### Justification of sample size

In phase 1b, we will use an adaptive Bayesian design in order to minimize the number of subjects to be included. Because of the characteristics of the continuous reassessment method with Bayesian inferences, the inclusion of 30 subjects has been found to suffice for studies of this kind [49, 50]. Stopping rules will be applied sequentially to stop further inclusions before this number is reached. In phase 2b, the expected number of participants is arbitrary because it depends on the opportunities for recruitment at all the centers involved in the study, and the lack of knowledge about the success rate of riluzole is likely to result in a sample size which is too large for a frequentist approach to be used. The number of participants included during 24 months will be 30 participants per randomized group (i.e., 60 patients in all). Participants in phase 1b might also participate in phase 2b.

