### Trial protocol

The timeline of the trial summarized in **Fig 1** will be the same in both 2 phases of the study. Subjects will participate for up to 5 weeks. The first 2 weeks will constitute the screening period, starting on the day the subject signs the Informed Consent Form. At the end of the screening period, participants will be randomized (1:1) to either the riluzole or the placebo groupsfor a 2-week period of treatment. Block randomisation stratified per center will be performed. A 1-week post-treatment period will ensue. It is planned to carry out three follow up visits on each participant: on day 3 after the beginning of treatment, at the end of the 2-week period of treatment, and one week after withdrawal of the medication. Details of the assessments and interventions occurring at each visit are presented in **Fig 1**.

At the screening visit, experimental drugs prepared by the coordinating pharmacy will be distributed to the investigating pharmacy at each study site. For phase 1b, riluzole oral suspension (5 mg/ml) will be prepared in 300 ml vial + syringe. For phase 2b, riluzole oral suspension will be diluted in Orablend SF* with a view to administering the same volume (20 ml) of oral suspension to each group. The investigating pharmacy will prepare clinically indiscernible galenic forms of riluzole and placebo. After being prescribed by the investigator, the treatments will be dispensed to patients at the second visit. All the documents required for drug traceability will be completed by the investigating pharmacist. The pharmacist will report the name of the drug, the dosage and the specific number of allocated drugs dispensed to each patient.

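### The stated rule for group comparisons names no centre or baseline term, although randomisation is stratified by centre and a baseline is defined; at 30 per arm this may cost precision on the continuous secondary outcomes

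*Protocol article*

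**What the plan says.** The Statistical analysis section of the protocol article gives one general rule for comparing groups: "Inter-group comparisons will be conducted using parametric or non-parametric tests, depending on the nature and the distributions of the variables". The threshold goes with it: "Unless otherwise specified, statistical significance is defined here as p<0.05". No covariate, stratum or model is attached to that rule.

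The same section separates the primary phase 2b analysis from the rest. For the primary, "the probability of a response being associated with the minimum effective dose will be estimated using a Bayesian approach according to a beta-binomial model", again with no covariate or stratum named. For the rest, "Secondary analysis and safety analysis will be performed by the CIC-CPCET". The rule on parametric and non-parametric tests therefore bears mainly on the secondary outcomes.

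The design supplies two things that the rule does not mention. Under Trial protocol: "Block randomisation stratified per center will be performed". Study design puts phase 2b at seven hospitals. Under Statistical analysis: "Baseline value will be the last value recorded before randomization". Outcome measures adds that the NRS is recorded in a diary every day of treatment.

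Justification of sample size sets phase 2b at 30 per randomised group, 60 in all, and calls the number arbitrary. It gives no power, effect size or standard deviation.

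**The concern.** Randomising within centre makes the arms alike on centre. If centre predicts outcome, an analysis without centre leaves that variation in the error term, and the interval comes out wider than the design allows. The same holds for baseline: where it correlates with the Week 2 value, leaving it out wastes information already collected.

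With 60 patients the loss matters more than in a large trial. Because the sample size is not tied to a power calculation, there is no stated margin to absorb it. Several secondary outcomes are scores or continuous measurements, such as the pain scale, the neuropathic pain total, the independence measure and the H-reflex ratio, and for these an adjusted analysis is straightforward.

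A secondary issue is interpretation. If the test is chosen outcome by outcome from the distribution, the quantity compared can move between a difference in means and a shift in ranks. A single pre-specified model avoids that.

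**Working it through.** **The plan's own figure.** 2 × 30 = 60 for phase 2b, and 60 + 30 (phase 1b) = 90, which agrees with the target enrolment in the abstract. Nothing further can be reproduced, because no effect, standard deviation or power is given.

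**Inputs.** From the article: n = 30 per arm, 1:1 allocation, seven centres, significance at p < 0.05. Assumed: a two-sided test (sidedness is not stated), no dropout, equal variance at baseline and Week 2, and a baseline-to-Week-2 correlation r of 0.3, 0.5 or 0.7.

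**Without adjustment, final scores.** In units of the outcome's SD:
- Difference detectable with 80% power: (1.960 + 0.842) × √(2/30) = 0.72.
- 95% interval half-width: 1.960 × √(2/30) = 0.51.

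**With baseline.** Relative to a final-score comparison, a change-score comparison has variance 2(1 − r) and ANCOVA has 1 − r². ANCOVA relative to change is therefore (1 − r²) / [2(1 − r)] = (1 + r)/2. The equivalent n per arm is 30 divided by the relevant ratio.

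| r | 1 − r² | acts like, against final score | (1 + r)/2 | acts like, against change score |
|---|---|---|---|---|
| 0.3 | 0.91 | 30/0.91 = 33 | 0.65 | 30/0.65 = 46 |
| 0.5 | 0.75 | 30/0.75 = 40 | 0.75 | 30/0.75 = 40 |
| 0.7 | 0.51 | 30/0.51 = 59 | 0.85 | 30/0.85 = 35 |

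The detectable difference under ANCOVA is 0.72 × √(1 − r²), that is 0.69, 0.63 and 0.52 SD. For a true difference of 0.5 SD, power is:

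| r | final score | change score | ANCOVA |
|---|---|---|---|
| 0.3 | 49% | 37% | 53% |
| 0.5 | 49% | 49% | 61% |
| 0.7 | 49% | 71% | 77% |

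**With centre.** Seven centres add six terms. Residual degrees of freedom go from 60 − 2 = 58 to 52, which raises the critical t value by 0.25%; baseline takes one more. On top of treatment and baseline (57 degrees of freedom), the estimated residual variance is multiplied by (1 − R²) × 57/51, where R² is the share of the remaining variation that centre explains in the sample. This gives 1.006 at R² = 0.10 and 0.894 at R² = 0.20. Six irrelevant terms would explain about 6/57 = 10.5% by chance, so on average the factor is close to 1 when centre does not matter and falls below 1 when it does.

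**Choice of test from the data.** A Shapiro pre-test followed by a t test or a Mann-Whitney test was simulated at 30 per arm with no true difference (2,000 runs per distribution). The type I error was 0.053 for normal data, 0.052 for lognormal data and 0.049 for rounded 0–10 scores.

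**The case against.** The strongest reply is that this is a journal article, and that covariates and strata are commonly left to the full protocol or the analysis plan, neither of which is shown. That stands as a limit. A reader might infer that the trial will run unadjusted analyses and ignore its strata; the article says neither. What remains is that the article does state a method of comparison, and a better one can be named in its place.

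A reader might also carry the point over to the primary outcome. The test rule does not govern it, and primary success is itself a change from Week 0 to Week 2, so baseline already enters through the endpoint. Replacing the beta-binomial with a covariate-rich Bayesian logistic model would be a trade-off, not the correction of an error. In a simulation with a log odds ratio of 1.5 and seven unequal centres, full adjustment moved power from 65% to 67% with moderately prognostic covariates and from 54% to 61% with strong ones. When the covariates were not prognostic, fixed centre effects lowered it from 77% to 73%.

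The article does not say whether secondary tests use final or change scores, so the larger gains in one column cannot be claimed alone. At r = 0.6, for example, 30 acts like 47 against final scores but 37.5 against change scores.

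Choosing tests by distribution might suggest an inflated error rate. The simulation does not show one, and part of that choice, the nature of the variable, is known in advance.

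Finally, a reader might conclude that NRS success rests on one noisy day. Only baseline is fixed as a last value; how the Week 2 value is derived is not stated. New averaging windows and extra pre-randomisation diary days would change the primary endpoint of a trial already in progress.

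**Conclusion.** The point holds for the continuous secondary outcomes of phase 2b and should be raised as an improvement to a stated method, not as an error that invalidates the trial. The article fixes stratification by centre and a baseline value, and its rule for comparing groups names neither.

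The direction of the gain is secure; the size is conditional. Over assumed correlations of 0.3 to 0.7, baseline adjustment is worth between 3 and 29 extra patients per arm against final-score tests, and between 5 and 16 against change-score tests. It applies only to outcomes with a baseline value and about 30 patients per arm. Surface EMG, done at experienced centres only, will have fewer. The global impression of change is rated only as change since joining, so it has no baseline to adjust for.

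The documents do not support a claim about type I error, a different primary model, or a loss figure presented as the trial's own.

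**What to change.** 1. For each continuous secondary outcome measured at baseline, pre-specify ANCOVA of the Week 2 value on treatment, baseline and centre, whatever the observed distribution. Report the adjusted difference with its 95% interval, and use rank-based ANCOVA as the sensitivity analysis. If the analysis plan already says this, a sentence in the article pointing to it is enough.
2. Keep the beta-binomial as the primary phase 2b analysis. Add one centre-adjusted sensitivity analysis, for example a Bayesian logistic model with treatment and a random centre effect. A random effect avoids spending six fixed terms on a binary outcome with about 60/7 = 9 patients per centre.
3. If the daily NRS is used further, limit it to a sensitivity analysis of the diary already collected. Averaging 14 days instead of one would give a variance ratio of 0.54, 0.72 or 0.91 at assumed between-day correlations of 0.5, 0.7 or 0.9. It would also change the question to the average effect over treatment, which should be stated.

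The cost is analysis wording and up to seven degrees of freedom (six for centre, one for baseline). No new data, visits or patients are needed. The changes should be fixed before any unblinded phase 2b comparison.

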### Study design

RILUSCI is an adaptive phase 1b–2b trial conducted on spastic patients with chronic SCI in order to determine the potential benefits of administering riluzole as compared with placebo. The protocol has been designed in keeping with the SPIRIT and CONSORT statements (see S1 Checklist: CONSORT 2010 and S2 Checklist: SPIRIT 2013 checklist). The SPIRIT schedule on enrolment, interventions and assessments is presented in **Fig 1**. **Fig 2** is a flowchart of the participants in the study based on the CONSORT guidelines [47].

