**Fig 2 pone.0276892.g002:**
[figure not shown]
CONSORT diagram.

Phase 1b will be a single-center double-blind trial involving a continuous reassessment method based on Bayesian inferences. The principle underlying this method is to identify the appropriate drug dosage required to obtain a level of efficacy which resembles as closely as possible a predetermined target level of efficacy in the population. The aim will be to determine the minimal effective dose (MED) of riluzole recorded in 75% of the patients tested. The phase 1 trial will be conducted at the Physical Medicine and Rehabilitation departments of Marseille’s public hospital group.

Phase 2b will be a parallel placebo-controlled multicentre randomised double-blind trial designed to compare the effects of a BID per os treatment with riluzole (daily dose to be defined during Phase 1b) *versus* placebo in participants with chronic SCI. Double-blind conditions will apply to both participants and investigators. The phase 2b trial will be conducted at 7 hospitals all over France. The participating centres include the Physical Medicine and Rehabilitation departments of Marseille’s public hopitals and the Valmante University Institute of Rehabilitation in Marseille (UGECAM), the University Hospitals of Limoges, Montpellier, Nantes, the Propara Rehabilitation centre in Montpellier, and the Saint Martin Rehabilitation Centre in Marseille.

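### The only analysis stated specifically for phase 2b is a one-arm response estimate at the minimal effective dose, although phase 2b is designed as a randomised comparison with placebo

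*Protocol article*

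**What the plan says.** Study design states the aim of the trial as "to determine the potential benefits of administering riluzole as compared with placebo". The same section describes phase 2b as a parallel, placebo-controlled, randomised, double-blind trial "designed to compare the effects of a BID per os treatment with riluzole" against placebo. Trial protocol gives 1:1 allocation, and Justification of sample size gives 30 participants per randomised group, 60 in all. Outcome measures makes the primary outcome binary: success on the Modified Ashworth Scale or on the spasticity NRS between Week 0 and Week 2.

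Statistical analysis contains one sentence on how phase 2b will be analysed: "the probability of a response being associated with the minimum effective dose will be estimated using a Bayesian approach according to a beta-binomial model". The next sentence, which names no phase, is "Statistical analyses will be performed sequentially per participant at the end of the 2-week assessment period".

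Earlier in that section are general statements: "Inter-group comparisons will be conducted using parametric or non-parametric tests, depending on the nature and the distributions of the variables" and "Unless otherwise specified, statistical significance is defined here as p<0.05". The work is also divided. One unit performs the Bayesian analysis, and for another the text says "Secondary analysis and safety analysis will be performed by the CIC-CPCET".

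Justification of sample size calls the phase 2b number arbitrary. It adds that, with riluzole's success rate unknown, a frequentist approach would probably need too large a sample.

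**The concern.** A placebo-controlled phase is run because response on the drug alone does not show a drug effect. The quantity named for phase 2b, the response probability at the chosen dose, contains no placebo term, no difference and no probability of superiority. It is the quantity that phase 1b targets, carried into a phase with a different purpose.

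The primary endpoint makes this matter. Success can be reached by either of two routes: a scale scored by the participant, or a resistance judged by the rater. Some success on placebo is therefore plausible, although the article gives no placebo rate. If the conclusion rested on the riluzole estimate, a high response in both arms could be read as efficacy. If it rested on a p<0.05 test instead, the article would hold two candidate primary analyses without saying which one decides.

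**Working it through.** **Plan's own figures.** The phase 2b size cannot be reproduced, because the article gives no effect size, placebo rate, power or decision rule. Only the total can be checked: 30 (phase 1b) + 2 × 30 (phase 2b) = 90, which agrees with the target enrolment in the Abstract. No stated number is wrong. The point concerns which quantity is estimated.

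**Does another sentence supply the contrast?**
- The between-group sentence is general. It names neither phase 2b nor the primary endpoint.
- The p<0.05 criterion is a default that gives way where something else is specified, and the phase 2b sentence specifies a Bayesian model.
- The sample size section moves phase 2b away from a frequentist approach.
- The Bayesian work and the secondary and safety work go to different units, and only the Bayesian work is linked to the phase 2b response.

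A contrast is therefore possible under the text, but it is not named as the primary one.

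**Illustration.** Inputs from the article: 30 per arm, binary outcome, beta-binomial model. Assumed: Beta(1,1) priors, the success counts, the true rates and the thresholds.

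*One-arm estimate.* With x successes in 30 the posterior is Beta(1 + x, 31 − x). For x = 22 it is Beta(23, 9), with mean 23/32 = 0.72 and 95% credible interval 0.55 to 0.86. The placebo count does not enter.

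*Two-arm contrast.* Use an independent posterior in each arm. The mean difference is (1 + xR)/32 − (1 + xP)/32, and Pr(pR > pP) is obtained by numerical integration.

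| Riluzole | Placebo | Mean difference | Pr(pR > pP) |
|---|---|---|---|
| 22/30 | 12/30 | 23/32 − 13/32 = 0.31 | 0.995 |
| 22/30 | 18/30 | 23/32 − 19/32 = 0.125 | 0.86 |
| 22/30 | 20/30 | 23/32 − 21/32 = 0.06 | 0.71 |
| 22/30 | 22/30 | 0 | 0.50 |

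The riluzole result is identical in every row, yet the evidence of superiority runs from strong to none.

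*What a one-arm rule could do.* Take the rule Pr(pR > 0.5) > 0.975, which needs at least 21/30. When both arms truly respond at the same rate, so that there is no drug effect, it is met with probability Pr(X ≥ 21), where X is Binomial(30, p): 0.18 at 60%, 0.59 at 70% and 0.80 at 75%. The article does not state this rule. It only shows why a one-arm quantity cannot carry the conclusion.

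*What a two-arm rule would do.* Take Pr(pR > pP) > 0.975 at one final analysis, 30 per arm, enumerating all 31 × 31 outcomes. With equal true rates between 30% and 75%, superiority is declared with probability 0.024 to 0.026. With riluzole at 75% (the phase 1b target, borrowed here), it is declared with probability 0.80, 0.52 or 0.23 for placebo at 40%, 50% or 60%.

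**The case against.** The strongest reply is that the same section does plan between-group comparisons. Phase 2b has only two groups, so such a comparison there means riluzole against placebo. No endpoint is excluded, and a division of labour between units does not show that the primary endpoint goes uncompared. A beta-binomial model can also be fitted in each arm and contrasted. Finally, this is a condensed article, and priors, thresholds and analysis sets commonly sit in a fuller document.

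Much of this stands. A reader might infer that the trial never compares riluzole with placebo, or that the randomised phase cannot answer its efficacy question. The article does not support either: between-group tests are planned, and 1:1 allocation with 30 per arm yields the data for a contrast. Nor is the absence of priors or a threshold a fault in itself.

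What the reply does not remove is that the quantity named for phase 2b belongs to one arm and does not match the stated comparison. An analysis plan that named the difference would still leave this sentence to be reconciled.

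A second tempting inference is that analysis after each participant inflates the false-positive rate. Simulating the two-arm 0.975 rule under no effect, with looks from participant 10 to 60, gave about 10% to 12%. That holds only if efficacy could be claimed at any look. The article states no such rule, its stopping rules are described for phase 1b, and updating a posterior is not in itself a claim. The figure is not a property of the plan as written.

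**Conclusion.** The concern holds in a limited form. The only analysis stated specifically for phase 2b estimates response at the minimal effective dose, while Study design defines that phase as a comparison with placebo. The general tests do not clearly fill the gap, because they are not linked to the primary endpoint and sit beside a text that turns away from a frequentist approach for this phase.

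The size can only be illustrated. For one and the same riluzole result, 72% with interval 55% to 86%, the probability of superiority ranges from 0.995 to 0.71 as placebo successes go from 12 to 20 of 30. This rests on assumed Beta(1,1) priors and assumed counts. The mismatch itself rests on the text alone and needs no assumption.

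**What to change.** Reconcile Study design with Statistical analysis by restating the phase 2b analysis, for example: *The primary analysis of phase 2b is the posterior distribution of the difference in success probability, riluzole minus placebo (pR − pP), from a beta-binomial model in each randomised arm. It is reported with its 95% credible interval. Superiority is concluded if Pr(pR > pP) exceeds a pre-set threshold, applied once after all 60 participants have completed Week 2.* A threshold of 0.975 with Beta(1,1) priors would give a type I error of about 2.5% with 30 per arm. The response estimate at the minimal effective dose can stay as a descriptive result.

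Tie the general between-group tests to the endpoints they serve, so that only one analysis of the primary endpoint decides.

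State whether the per-participant sequential analysis applies to phase 1b only. Only if efficacy could be claimed at interim looks in phase 2b would the threshold need calibration by simulation.

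The cost is protocol and analysis-plan wording. No further participants, visits or data are needed.
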